#### SECONDARY OUTCOME MEASURES

##### **Objective 2 – Evaluate provider acceptability of the RAMP through utilization measures.**

Each report that the provider completes to document review of a report will be available in the RAMP platform along with a timestamp of submission. The research coordinators will verify that requests have been distributed through the RAMP platform. Only data reviewed by providers without research coordinator prompting will count towards the proportion of reports reviewed. If outreach is provided by research coordinator or Study PI, this will occur outside of the time window outlined in the endpoints and will be for the purposes of ensuring good patient care. The secondary endpoint, proportion of provider review surveys with at least one available RAMP Report where review is documented, is only relevant to the subset of participants randomized to the RAMP intervention group. There is no formal hypothesis testing for this secondary objective.

### 8.2 SAFETY AND OTHER ASSESSMENTS

Because this study is of an educational intervention, adverse events (AEs) and serious adverse events (SAEs) are not expected. While the study team will not solicit AEs or SAEs, the study team will provide all participants with a telephone number to report AEs/SAEs. AEs and SAEs will be collected for all participants.

### 8.3 ADVERSE EVENTS AND SERIOUS ADVERSE EVENTS

#### 8.3.1 DEFINITION OF ADVERSE EVENTS (AE)

An AE is defined as any untoward occurrence associated with the use of an intervention in humans, whether or not considered intervention related (21 CFR 312.32 [a]). Stable chronic conditions that present prior to enrollment and do not worsen are not considered AEs but will be accounted for in the participant's medical history. Exacerbation or worsening of pre-existing conditions are defined as AEs. Reported AEs will be reviewed and classified by the investigator. We will only record and track severe, serious, and AEs related to the study

intervention. Expected AEs are listed below (8.3.3.3). This study is only reporting AEs for the child participant due to the negligible risk to providers and caregiver participants.

---

### 8.3.2 DEFINITION OF SERIOUS ADVERSE EVENTS (SAE)

We will consider an AE or suspected adverse reaction “serious” if, in the view of the PIs, medical monitor, DSMB, or sponsor, it results in any of the following outcomes:

- Death
- Life-threatening AE
- Inpatient hospitalization or prolongation of existing hospitalization
- Persistent or significant incapacitation or substantial disruption of the ability to conduct normal life functions
- Congenital anomaly/birth defect.

Important medical events that may not result in death, be life-threatening, or require hospitalization may be considered serious when, based upon appropriate medical judgment, they may jeopardize the participant and may require medical or surgical intervention to prevent one of the outcomes listed in the SAE definition.

---

### 8.3.3 CLASSIFICATION OF AN ADVERSE EVENT

The investigator or qualified sub-investigator is responsible for assessing all AEs for causality and severity, and for final review and confirmation of accuracy of event information and assessments.

---

#### 8.3.3.1 SEVERITY OF EVENT

These are the guidelines to describe the severity of AEs:

**Mild.** Events require minimal or no treatment and do not interfere with the participant’s daily activities.

**Moderate.** Events result in a low level of inconvenience or concern with the therapeutic measures. Moderate events may cause some interference with daily functioning.

**Severe.** Events interrupt a participant’s usual daily activity and may require systemic drug therapy or other treatment. Severe events are usually potentially life-threatening or incapacitating. Of note, the term “severe” does not necessarily equate to “serious.”

---

#### 8.3.3.2 RELATIONSHIP TO STUDY INTERVENTION

All AEs and SAEs must have their relationship to trial intervention assessed by the clinician who examines and evaluates the participant based on temporal relationship and her/his clinical judgment. We will grade the degree of certainty about causality by using the categories below.

**Related.** We know the AE occurred with the trial intervention, there is a reasonable possibility that the trial intervention caused the AE, or there is a temporal relationship between the trial intervention and event.

Reasonable possibility means that there is evidence to suggest a causal relationship between the trial intervention and the AE.

**Not Related.** There is not a reasonable possibility that the administration of the trial intervention caused the event, there is no temporal relationship between the trial intervention and event onset, or there is an established alternate etiology.

---

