| Receive digital handouts (control arm only)                                 | X                     |          |           |
| Allow access to clinical baseline assessment and complete study assessments | X                     |          |           |

|                           |   |  |   |
|---------------------------|---|--|---|
| RAMP platform orientation |   |  | X |
| Best practice education   |   |  | X |
| Review RAMP reports       |   |  | X |
| Complete Provider Survey  |   |  | X |
| Receive Compensation      | X |  | X |

| Participant Activities                                                                 | Day -35—Day 0 | Day 0 | Day 1-28 | Day 29-90  | Day 90
(-30/+15)** |
|----------------------------------------------------------------------------------------|---------------|-------|----------|------------|-----------------------|
| Pre-study visit with provider* (ADHD diagnosis made, stimulant started)                | X             |       |          |            |                       |
| Research coordinator contacts and eligibility screen, principal investigator review    | X             |       |          |            |                       |
| Enrollment and informed consent                                                        |               | X     |          |            |                       |
| Randomized                                                                             |               | X     |          |            |                       |
| Diagnostic Assessment requested from provider                                          |               | X     |          |            |                       |
| RAMP Report request (caregiver and teacher) for intervention group only                |               |       | Weekly   | Monthly*** |                       |
| Digital education handout (control group only)                                         |               |       | Weekly   | Monthly*** |                       |
| Study Assessments (not used in clinical management; retention measure) |               |       |          |            | X                     |

\*Caregiver/child participant dyads will be enrolled within 5 weeks (35 days) of the child being prescribed stimulants.

\*\*The window for the 90-day Study Assessment is -30 days to +15 days. Study Assessments must be received by the study team within this window.

\*\*\*Each monthly period is defined as 28 days.

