## 5 STUDY POPULATION

### 5.1 INCLUSION CRITERIA

**Caregiver/child dyad eligibility:** To be eligible to participate in the trial, caregiver/child dyads must attend one of the four participating primary care clinics and meet the following inclusion criteria:

The child must

- be under the care of a participating provider
- be aged 5-11 at enrollment
- have a diagnosis of ADHD
- be initiating stimulant medication for treatment for the first time or have not received stimulant medication for the last 3 months
- be attending in-person elementary school

Primary caregiver must

- be willing and legally able to give consent
- have access to a smartphone
- be English-speaking
- reside with the child at least 3 days per week
- complete an initial symptom assessment prior to starting stimulant treatment and be willing to provide a copy to the study team

Eligible children include those receiving a new ADHD diagnosis, those having a prior diagnosis without stimulant medication treatment, and those having a prior diagnosis but have not received stimulant medication for the last 3 months. Children only receiving adjunct (non-stimulant) medication are ineligible. Only one child per household can enroll. The participating caregiver is defined as the parent or legally authorized representative (LAR) who can consent for their child's medical treatment and should be with the child at least 3 days per week.

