#### 8.3.3.3 EXPECTEDNESS

The site investigators will be responsible for determining whether an AE or SAE is expected or unexpected.

An AE or SAE will be considered unexpected if the nature, severity, or frequency of the event is not consistent with the risk information previously described for the trial intervention.

Expected events could include the following: medication related side effects (sleep difficulty, appetite suppression, stomachache, headache) as well as new mental health diagnoses (depression, anxiety, suicide attempt, substance use disorder).

---

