### 9.4.4 SAFETY ANALYSES

The DCOC will detail reported intervention-related AEs and SAEs experienced by study participants and will summarize these by the intervention arm. The DCOC will present summary statistics for overall and by sites.

---

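### Related and Not Related overlap in section 8.3.3.2 with no order of precedence, so the same stimulant side effect can be coded either way and may count as intervention-related in the RAMP arm only

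*Protocol*

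**What the plan says.** Section 8.3.3.2 gives two grades of relationship to the trial intervention. *Related* has three alternative grounds, the last being "or there is a temporal relationship between the trial intervention and event". *Not Related* also has three, the last being "or there is an established alternate etiology". The examining clinician decides, "based on temporal relationship and her/his clinical judgment".

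The grade has two uses. Section 8.3.1 limits collection: "We will only record and track severe, serious, and AEs related to the study" (the sentence ends with the word intervention). Section 9.4.4 sets the analysis: "The DCOC will detail reported intervention-related AEs and SAEs experienced by study participants and will summarize these by the intervention arm".

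The setting makes the grading hard. Under section 5.1 the child must "be initiating stimulant medication for treatment for the first time or have not received stimulant medication for the last 3 months". The footnote in section 1.3 adds: "Caregiver/child participant dyads will be enrolled within 5 weeks (35 days) of the child being prescribed stimulants". Section 8.3.3.3 anticipates the resulting events: "Expected events could include the following: medication related side effects (sleep difficulty, appetite suppression, stomachache, headache"). Section 6.2 gives RAMP to the intervention arm and emailed handouts to the control arm.

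**The concern.** The events most likely to be reported are common stimulant effects, because every child is in the first weeks of a new or resumed stimulant and section 8.3.4 has providers remind caregivers to report medication side effects. These are the events that the two definitions cannot sort. The stimulant is common to both arms and RAMP is not, so a grade that can rest on coincidence in time with RAMP is open to one arm only on the plainest reading.

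A difference in intervention-related events could then reflect which clause a clinician applied. The data and safety monitoring board and the designers of the full-scale trial would have no means of telling that apart from a real effect.

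**Working it through.** No figure is stated in the plan and none needs reproducing. The check traces one event through the text.

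**Test event.** A mild headache, a recognised effect of the stimulant, beginning after Day 0.

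| Case | Related, by timing alone | Not Related, by alternate etiology | Grade under 8.3.3.2 |
|---|---|---|---|
| RAMP arm, onset after Day 0 | met | met | both |
| Control arm, trial intervention read as RAMP | not met, no RAMP exposure | met | Not Related |
| Control arm, handouts read as part of the trial intervention | met | met | both |
| Either arm, onset before Day 0 | not met | met | Not Related |

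The first row is the overlap. The first two rows together are the asymmetry between arms. The fourth row is a limit: a stimulant may be prescribed up to 35 days before enrollment, so some effects begin before any RAMP exposure.

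**Recording.** Under 8.3.1 a mild or moderate event is kept only if related, so in the first row the choice of clause decides whether the headache enters the database. Severe events and SAEs are kept under 8.3.1 and followed under 8.3.4 whatever the relationship; for them only the label is at stake. The collection rule is itself worded three ways: related to the study intervention (8.3.1), related to study procedures (8.3.4), and potentially related (8.3.5). Section 8.3.4 also has the site capture all AEs on the case report form.

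**Summary.** Section 9.4.4 names intervention-related AEs and SAEs by arm. It does not mention severe, non-serious, unrelated AEs, although 8.3.5 places severe AEs in the statistical analysis.

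**Size.** Let *r* be the proportion of children with a non-severe stimulant effect beginning after Day 0, and *a* the proportion of those that reach the site. Both are assumed equal in the two arms. With 18 children per arm (9.2):

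- Timing clause governs, trial intervention read as RAMP: 18 × *r* × *a* in the RAMP arm, 0 in control.
- Alternate-etiology clause governs: 0 in each arm.

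The documents give neither *r* nor *a*. Purely as an illustration, *r* of 20% to 50% and *a* of 25% to 75% give 18 × 0.20 × 0.25 = 0.9 to 18 × 0.50 × 0.75 = 6.75 children on the first branch, and 0 on the second. The text permits either branch or a mixture of them.

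**The case against.** A reader might infer that the by-arm summary is skewed by rule, with stimulant effects necessarily booked to RAMP. The documents do not support that:

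- The same section makes an established alternate etiology sufficient for *Not Related*, 8.3.3.3 calls these effects medication related, and the clinician uses judgment. A careful site could record none in either arm.
- An empty control column is not certain either. Section 6.1.1 describes the handouts under the study intervention heading, and the study-procedures wording of 8.3.4 could reach control children.

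A reader might also infer that any excess in the RAMP arm would be a false signal. That does not follow. Sections 1.1 and 2.3.2 expect RAMP to speed titration, so side-effect rates could truly differ because of RAMP. For the same reason the remedy should not declare every stimulant-explained event unrelated. With 8.3.1 unchanged, that would remove non-severe effects from both arms and hide a difference caused by faster titration.

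It can fairly be added that this is a minimal-risk pilot with an independent medical monitor and a monitoring board, that the AE summary involves no test, and that table layout belongs to the SAP. This limits the importance of the point but does not remove the overlap. The definitions and the recording rule are fixed in the protocol, and an SAP cannot restore events that were never recorded.

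One feature points the other way. Section 1.1 puts a side-effect query in the RAMP Report, sent about six times (weekly for 4 weeks, then monthly for 2 months), and the protocol describes no such query for control. Section 8.3.4 names RAMP Reports as a route by which an SAE may come to notice. Events may therefore surface more often in the arm where the timing clause can apply, although the footnote in 1.3 limits what coordinators abstract from those reports.

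**Conclusion.** The point holds as a defect of definition. *Related* and *Not Related* are not mutually exclusive and no precedence is stated. Because the grade feeds both the recording of non-severe events and the by-arm summary, the same stimulant side effect can be counted in the RAMP arm and left out in control.

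The size of any distortion cannot be derived from the documents. It is nil if alternate etiology governs. At the other extreme it covers all non-severe stimulant effects reported after Day 0 in the RAMP arm, if timing governs and the trial intervention means RAMP alone. The illustrative counts rest on assumed rates and are not an estimate.

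Severity is minor to moderate. The AE summary is descriptive, severe AEs and SAEs are collected regardless of relationship, and neither the primary nor the secondary endpoint is affected.

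**What to change.** - **8.3.3.2.** Delete the ground that rests on timing alone. Let *Related* require a reasonable possibility that study procedures caused the event, including through management prompted by RAMP, as the investigator judges. Reword the first ground too, since it can be read as mere co-occurrence. Define *Not Related* as the complement, and apply the same definition in both arms.
- **8.3.1, 8.3.4 and 8.3.5.** Reconcile the three collection rules, so that recording of a non-severe AE does not depend on a label that only one arm can receive.
- **AE form.** Add a field for attribution to the background stimulant, completed for every recorded AE in both arms.
- **9.4.4.** Summarize all severe AEs and SAEs by arm regardless of relatedness, and list related AEs separately.

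The cost is protocol wording, one form field, and a minor re-review of any AEs already classified. No treatment or endpoint changes.

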#### 8.3.3.3 EXPECTEDNESS

The site investigators will be responsible for determining whether an AE or SAE is expected or unexpected.

An AE or SAE will be considered unexpected if the nature, severity, or frequency of the event is not consistent with the risk information previously described for the trial intervention.

Expected events could include the following: medication related side effects (sleep difficulty, appetite suppression, stomachache, headache) as well as new mental health diagnoses (depression, anxiety, suicide attempt, substance use disorder).

---

#### 8.3.4 TIME PERIOD AND FREQUENCY FOR EVENT ASSESSMENT AND FOLLOW-UP

The study team will collect severe AEs, SAEs, and AEs related to study procedures. The study team will provide participants with a site-specific telephone number to report AEs, but will not actively solicit AEs or SAEs. The occurrence of a SAE may come to the attention of study personnel during clinical visits, by the clinical team with administration of RAMP Reports, or by the medical monitor upon reviewing data. The site study team will capture all AEs on the appropriate case report form following the instructions and timelines provided in the MOP. Information to be collected includes event description, date/time of onset, date/time of resolution, clinician's assessment of severity, relationship to study intervention and time of resolution/stabilization of the event. Site study teams must follow all severe and SAEs, regardless of relationship, until there is resolution, the condition stabilizes, the event is otherwise explained or is judged by the protocol study team to be no longer clinically significant, or the participant is lost to follow-up.

Clinic providers participating in this study will be asked to remind caregiver participants to report any medication side effects or events that caused them to seek medical assistance or hospitalization for their child to the study team.

---

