## 1 PROTOCOL SUMMARY

### 1.1 SYNOPSIS

**Title:** A Pilot Study of a Remote Attention-Deficit/Hyperactivity Disorder Monitoring Program (RAMP) for Children in Rural Areas

**Study Description:** This is a pilot study examining the use of an Attention-Deficit/Hyperactivity Disorder (ADHD) Monitoring Program during the early stages of treating ADHD in children living in rural settings. The Remote ADHD Monitoring Program (RAMP) will include provider ADHD Best Practice education, caregiver and teacher prompts for frequent RAMP Reports of inattention and hyperactivity symptoms and a provider dashboard with enrolled children. The RAMP Report includes the publicly available Vanderbilt Rating Scales (henceforth shortened to Vanderbilt Assessment), which is a commonly used, guideline-recommended tool for both diagnosis and management of ADHD for use by parents and teachers. See Appendix 1. This assessment was initially validated in a referral population with teacher reporters in 1998 and with parent reporters in 2003, and subsequently in a community population with both

Remote ADHD Monitoring Program (RAMP) Report includes:

- Inattention and hyperactivity questions from Vanderbilt assessment (18 total)
- Medication side effects query
- School performance query
- Behavior health provider visits query

reporters in 2013. Additionally, school performance, medication side effects and behavioral therapy engagement will be solicited on a recurring basis. The results of this pilot will be used to design a full-scale efficacy trial in additional rural sites to expand diversity and assess generalizability.

For this pilot study, children diagnosed with ADHD starting stimulant treatment for the first time in rural settings will be the focus of efforts to improve time to optimal symptom control, in an effort to maximize the treatment benefit for the academic year. We anticipate that more frequent provision of information by families and teachers to medical providers, enabled by technology and remote monitoring tools, will encourage more rapid improvement in symptom burden. This would be achieved through timely, even weekly, titration of medication per the current treatment guidelines, which is only possible with symptom reports.

The goals of this pilot study are 2-fold:

- Evaluate caregiver and teacher utilization of the RAMP platform early in the treatment course of ADHD

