| Description of Sites Enrolling Participants: | A total of 4 practice locations will be selected from two ISPCTN awardee sites, with each site recruiting at least 1 practice location for participation. Practices should care for at least 700 patients aged 5-11 years and should regularly diagnose and manage pediatric ADHD. Practices                                                                                                                                                                                               |                                                                                                                                                                                                                                                                                                                                               |

will be designated as rural if they are at least 30 minutes travel distance from a pediatric academic medical center (similar to prior studies) and are located in a city with fewer than 50,000 people. Practices will be designated as underserved if at least 40% of its pediatric patient visits are covered by Medicaid.

The staff at the selected practices are not directly involved in the design, execution, or analysis of this research study and are thus considered not engaged in research activities. However, practice personnel may carry out specific, limited supportive tasks as directed by the site study team, provided these tasks remain appropriately constrained in scope.

**Description of Study Intervention:** The intervention group will be enrolled in the RAMP. The RAMP platform used for this study will be an adaptation of an existing program and will be housed in REDCap, a HIPAA-compliant data collection tool. Caregivers and teachers will receive text-based requests for reports with embedded links to select radio button questionnaires directly on their mobile device (without any login requirement). Questions include current inattention/hyperactivity symptoms, school performance, and any engagement in behavioral therapy. These areas of information are typically considered by providers to aid in decision making regarding medication dose adjustments. Inattention/hyperactivity symptom questions and scoring is taken directly from the Vanderbilt Assessment. These requests for information will be distributed weekly for 4 weeks, then monthly for 2 months.

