### 1.3 SCHEDULE OF ACTIVITIES (SOA)

|                                                                | Anticipated Study Period (in Months) |   |               |    |    |    |    |    |    |
|----------------------------------------------------------------|--------------------------------------|---|---------------|----|----|----|----|----|----|
| Study Level Activities                                         | 1                                    | 2 | Months 3 - 11 | 12 | 13 | 14 | 15 | 16 | 17 |
| Provider ADHD and study education                              | X                                    |   |               |    |    |    |    |    |    |
| Provider consent                                               | X                                    | X |               |    |    |    |    |    |    |
| Caregiver/child enrollment, consent, and randomization         |                                      | X | X**           |    |    |    |    |    |    |
| Participant on-study activity                                  |                                      | X | X             | X  | X  | X  |    |    |    |
| Chart and RAMP review and abstraction* by research coordinator |                                      | X | X             | X  | X  | X  |    |    |    |
| Analysis and write-up                                          |                                      |   |               |    |    |    | X  | X  | X  |

\*The information gathered from chart review and RAMP reports will not exceed the presence/absence of the paper symptom form/RAMP report, the date/time they were submitted, and whether or not they were reviewed by a provider.

\*\*Enrollment will pause for 3 months during the summer months when children are out of school.

| Study Activities                                                            | Caregiver/Child Dyads | Teachers | Providers |
|-----------------------------------------------------------------------------|-----------------------|----------|-----------|
| Informed consent                                                            | X                     |          | X         |
| Randomization                                                               | X                     |          |           |
| Complete RAMP reports (intervention arm only)                               | X                     | X        |           |

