|-----------|---------------------------|-----------------------|--------------------|------------------|-------------|------------------|-------------|------------------|-------------|------------------|
| 11 Test1  | 1 view    |                       |                    |                  |             |                  |             |                  |             |                  |
| 12 Test2  | None view |                       |                    |                  |             |                  |             |                  |             |                  |
| 13 Test3  | None view |                       |                    |                  |             |                  |             |                  |             |                  |
| 14 Test4  | None view |                       |                    |                  |             |                  |             |                  |             |                  |

**RAMP Platform Prototype. A prototype of the dashboard that providers and research coordinators will use to review participant-entered data and monitor study activities, respectively**

The reports submitted by caregivers will be found on a different tab than those submitted by a teacher (but linked with the same ID) to clearly identify source. Providers and research coordinators will review RAMP Reports from a dashboard similar

to the figure on the right. A red dot will indicate an unreviewed RAMP Report has been entered by the participant. The provider will select the red dot to open the report from the caregiver or teacher. Following review, the provider will answer a quick 2-question, radio-button style survey regarding their response to the report. Research coordinators will be able to monitor data entry, and review and document clinical changes as a result of the report.

**Digital Education Handouts:** Digital education handouts will be sent to all caregivers in the control group on a weekly basis for 4 weeks, then monthly for 2 months. These will be sent through email, and will cover a range of general pediatric topics, such as nutrition, exercise, and screen time.

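### Only the RAMP arm gets scheduled medication side-effect queries, so adverse event counts by arm are not comparably ascertained, and the protocol leaves unclear what a coordinator may record from RAMP Reports and charts

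*Protocol*

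**What the plan says.** **Asking.** The Section 1.1 list of RAMP Report contents includes "Medication side effects query", and the text there adds that "school performance, medication side effects and behavioral therapy engagement will be solicited on a recurring basis". Requests are "distributed weekly for 4 weeks, then monthly for 2 months". The activities table in Section 1.3 confines RAMP Reports to the intervention arm. Controls use paper symptom forms on a schedule set by their provider (Section 1.1) and receive general health handouts by email (Section 6.1.1).

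**Stated policy on events.** Section 8.2 reads "While the study team will not solicit AEs or SAEs" and goes on to offer all participants a telephone number for reporting. Section 8.3.4 repeats that events are not actively solicited. It then names several routes by which a serious event may surface, among them "by the clinical team with administration of RAMP Reports, or by the medical monitor upon reviewing data". It closes by having clinic providers remind caregivers to report side effects and events that led to medical care.

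**Recording.** Section 8.3.1 restricts tracking to severe, serious and related events. Section 8.3.3.2 lets a temporal relationship alone qualify an event as related. A Section 1.3 footnote, attached to the coordinator's chart and RAMP review, states "The information gathered from chart review and RAMP reports will not exceed the presence/absence of the paper symptom form/RAMP report", plus date and time of submission and whether a provider reviewed it. Section 6.1.1, by contrast, has coordinators "review and document clinical changes as a result of the report".

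**Analysis.** For reported intervention-related adverse events and serious adverse events, Section 9.4.4 says that the coordinating center "will summarize these by the intervention arm".

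**The concern.** When one arm is asked about side effects on a schedule and the other relies on volunteered reports, the first arm tends to show more events even if the true rates are equal. Section 2.3.2 gives more rapid medication titration as a possible benefit of RAMP, so stimulant side effects are the harm that planners of the full-scale trial will look for in the pilot. A higher count in the RAMP arm could reflect more asking, and a low count in control could reflect less. No analysis plan can repair this afterwards if the route by which each event was detected was never recorded.

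The second issue is practical. A coordinator who reads a RAMP Report or chart and sees a reportable event finds one section that limits what may be gathered and others that point to documenting it. Two sites could reasonably act differently.

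**Working it through.** The protocol states no figure on this point, so there is none to reproduce. The check is a count of scheduled queries, an illustration of the possible distortion, and a comparison of sections.

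**1. Scheduled queries.** Weekly for 4 weeks plus monthly for 2 months gives 4 + 2 = 6 caregiver requests per dyad. With 18 dyads per arm (Section 9.2), 6 × 18 = 108 in the RAMP arm and 0 scheduled by the study in control. At the 52.7% return rate that Section 9.2 expects for RAMP Reports, about 0.527 × 108 = 57 would be answered. These counts rest on the Section 1.1 list. The description of the intervention later in Section 1.1, and the description of the caregiver report in Section 6.1.1, name the RAMP content without a side-effects item. Section 6.1.1 calls teacher reports identical to caregiver reports, yet says that they consist of the 18 symptom questions.

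**2. Possible distortion.** Let *s* be the probability that a recordable event reaches the study without any RAMP query. The protocol gives no value for *s*. Assume equal true risk in both arms, one RAMP request after each event, a returned report that always reveals the event, return independent of *s*, and a revealed event that is then recorded.

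- Control capture = *s*
- RAMP capture = 1 − (1 − *s*)(1 − 0.527)
- Apparent ratio = RAMP capture ÷ *s*; the true risk cancels

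| Assumed *s* | RAMP capture | Apparent ratio |
|---|---|---|
| 10% | 1 − 0.90 × 0.473 = 57.4% | 5.7 |
| 30% | 1 − 0.70 × 0.473 = 66.9% | 2.2 |
| 50% | 1 − 0.50 × 0.473 = 76.4% | 1.5 |
| 80% | 1 − 0.20 × 0.473 = 90.5% | 1.1 |

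In children rather than ratios: if 10% truly had a recordable event (an assumption; 1.8 per arm), the expected recorded counts would be 1.03 in RAMP against 0.18 in control at *s* = 10%, and 1.63 against 1.44 at *s* = 80%. The direction is stable under these assumptions; the size is not known.

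**3. Solicitation.** Section 1.1 has side effects solicited repeatedly, while Sections 8.2 and 8.3.4 say that adverse events are not solicited. The two can stand together only if the side-effects item is not a source of adverse events. But Section 8.3.4 treats RAMP Reports as a route by which serious events surface.

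**4. Recording.** The Section 1.3 footnote caps what coordinators gather at presence, timing and review status. Documenting clinical changes that result from a report (Section 6.1.1) goes beyond that cap. Section 8.3.4 has the site team record the description, onset, severity and relationship of adverse events. It does not say whether that duty overrides the footnote when the coordinator is the one who sees the event.

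**The case against.** Several points on the other side are sound and limit the finding.

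- **Recording is filtered.** Only severe, serious or related events are tracked, so most mild appetite loss, headache or poor sleep should not enter the table in either arm. Serious events such as hospitalization also depend less on a repeated questionnaire. The filter does not remove the imbalance, because a temporal relationship alone suffices for relatedness, and an effect noted in a RAMP Report could qualify on that basis.
- **Control families are not without a prompt.** The provider reminder and the telephone number apply to both arms. The reminder has no schedule, so the asking stays unequal.
- **Safety is not an objective.** Neither objective concerns it, no test of adverse events is planned, and 18 per arm could not settle comparative harm even with perfect ascertainment. What is affected is a descriptive summary.
- **The Section 6.1.1 wording may be narrower than it looks.** It follows the sentence on the provider's two-question survey and could refer to those answers. That is possible, but the text does not say so.

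Two stronger readings are tempting. A reader might infer from the footnote that side effects entered in RAMP can never reach the adverse event record. The documents do not support that. The footnote binds coordinator abstraction, whereas the route quoted from Section 8.3.4 runs through the clinical team and the medical monitor, and caregivers can still call. Detailed recording steps are left to the manual of procedures, which is not at hand. A reader might also settle on one inflation factor for the RAMP arm. The protocol gives no event rate or spontaneous capture rate, so only a range conditional on assumptions can be shown.

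**Conclusion.** The point holds as one of unequal ascertainment and unreconciled text. The RAMP arm has six scheduled side-effect queries per caregiver and control has none, so the Section 9.4.4 summary by arm is open to detection bias within the recorded subset of severe, serious or related events. Its size is unknown. Under the stated assumptions the apparent ratio with no true difference lies between 1.1 and 5.7, depending on a spontaneous capture rate that the protocol does not give. The count itself depends on Section 1.1 being right that the side-effects item is in the report.

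Separately, the Section 1.3 footnote and Section 6.1.1 conflict on what coordinators may document, and it is unclear whether an event that a coordinator sees in a RAMP Report or chart may be entered on the adverse event form. Clinicians and caregivers can still report it. Neither issue touches the primary or secondary endpoint. Both affect how far the pilot's safety table can inform the full-scale trial.

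**What to change.** 1. **Record the detection source of every adverse event and serious adverse event.** In Section 9.4.4, tabulate events first found through RAMP Reports separately, and label the counts by arm as not comparably ascertained. Cost: one field on the form and one extra table.
2. **Reconcile Sections 1.1, 1.3, 6.1.1, 8.2 and 8.3.4.** State whether the side-effects item is in the caregiver and teacher RAMP Reports, and whether the answers are a source of adverse events. Reword the Section 1.3 footnote so that a reportable event seen in a RAMP Report or chart may be entered on the adverse event form. The amendment log shows that the footnote answered an IRB contingency, so this needs an IRB amendment and is more than an editorial change.
3. **Optionally, equalise the asking.** Put one identical side-effect and medical-event question to both arms at the check-ins at about 1 week, 4 weeks and 2 months (Sections 5.5.3 and 7.3). Those contacts are described as technology and form-completion support, so first confirm that controls receive them. The no-solicitation statements in Sections 8.2 and 8.3.4 would have to be amended too. Cost: slightly longer calls and more events to classify.

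The first two steps suffice to make the safety summary interpretable; only the third reduces the imbalance in asking itself.
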